**Fig. 2 Fig2:**
[figure not shown]
District, school, and participant recruitment diagram for the FLEX study

## Interventions

The *100 Mile Club* is a school-based program that encourages children to walk, run, or wheel 100 miles over the course of the school year (approximately 3 miles per week). The program can be implemented before, during, and/or after school depending on the school schedule and is led by one or two champions (e.g., PE teachers), identified by school administration, who log student miles. Champions are encouraged to tally participants’ miles each week and display participant and school progress in a prominent location. The goal is to encourage participants and provide positive feedback and reinforcement. Champions are trained by study staff and are provided materials, resources, and ongoing support for implementation throughout the duration of the intervention.

*Just Move* is a program of structured classroom-based, PA breaks that integrates both high- and low-intensity movements (ex. jumping jacks, squats, stretches, yoga) with academic material to provide children with opportunities for engaging in PA while learning. Breaks are designed to be short (5–15 min), and teachers are encouraged to incorporate at least one break per day. *Just Move* activities are presented on cards with a picture of the movement and suggestions for connecting the moves with academic subjects like math, language arts, and science. Study staff train teachers to implement the activity breaks and provide a set of cards along with strategies and ideas for making the breaks fun and engaging for their students and low-burden for the teachers themselves. Study staff provide ongoing support to classroom teachers throughout the intervention to help ensure that teachers continue to implement *Just Move* breaks in their classrooms.

Both the *100 Mile Club* and *Just Move* program originated in schools and were identified by the Active Schools Acceleration Project (ASAP), a nationwide initiative dedicated to increasing the PA of U.S. schoolchildren [21, 22]. The *100 Mile Club* and *Just Move* were selected through a nationwide contest for school-based PA innovation in 2012, assessed for scalability and implementation potential, and currently take place in schools around the U.S. Both programs are low-cost, require minimal resources to implement, and are flexible and adaptable to a range of school environments. Teacher-developed and champion-led school-based PA programs may have unique advantages with respect to feasibility and sustainability, as opposed to programs developed by researchers outside of the school environment [23].

Control schools will receive a delayed intervention of either the *100 Mile Club* or *Just Move* after completion of the study (Wave 1 in Fall 2016; Wave 2 in Fall 2017).

### Student recruitment

Study staff conducted presentations in schools to explain the study and enrollment procedures, and to distribute recruitment materials to all 3rd and 4th grade students. Presentations were given assembly-style or in individual classrooms. Permission packets were sent home with each student and included: 1) a flyer with information about data collection procedures; 2) a plain language consent form for the parent/guardian; 3) a child assent form; and 4) a demographic form for the parent/guardian to complete. Permission packets were available in English, Spanish, Portuguese, Haitian Creole, Arabic, Vietnamese, and Mandarin, the primary languages spoken in targeted communities. Students were asked to return completed packets approximately 1 week after they were distributed. Enrollment was closed at the start of baseline data collection.

## Data collection methods

### Overview

Detailed information about study measures and time points is presented in Table 1.

**Table 1 Tab1:** Data collection plan for the FLEX Study

	Baseline (School Year 1)	Midpoint (School Year 1)	Post-Intervention (School Year 2)	Once per school year
Participant level measures				
Primary outcome measures				
Physical activity (accelerometry)	√	√	√	
Cognitive function (Digit Span and Stroop Color-Word tests)	√	√	√	
Standardized test scores	√^a^	√	√	
Attendance	√^a^	√	√	
Anthropometric measures				
Height	√	√	√	
Weight	√	√	√	
Additional physical activity measures				
Social support for PA	√	√	√	
What Kind of Kid Are You? (self-perception of behavior, athletic competence and global self-worth)	√	√	√	
Cardiorespiratory fitness (PACER)				√
Dietary measures				
Weekday breakfast consumption	√	√	√	
7-day dietary recall	√	√	√	
Demographic measures				
Date of birth	√			
Grade	√			
Sex	√			
Race/Ethnicity	√			
Free/reduced price lunch eligibility	√			
Behavioral/developmental difficulties	√			
Individualized education program status	√			
Maternal education level	√			
Paternal education level	√			
School-level measures				
School physical activity environment scan				√
School food environment scan				√
Program evaluation measures (100 Mile Club and Just Move schools)				
Participant-level program participation and attitudes		√	√	
Champion/teacher program questionnaire	√	√	√	
Direct observation				√

^a^Collected in the spring of the prior year

Briefly, child-level data collection takes place at each participating school during regular school hours at each of the three time points (baseline, midpoint, and post-intervention). Exceptions are demographic data, which are collected once at baseline, and fitness measurements, which are conducted at a separate time once per school year. Child-level standardized test scores for Math and English Language Arts (ELA) are collected from the Massachusetts Department of Elementary and Secondary Education (DESE) after testing is completed each spring. School-level data is collected once per year (physical activity environment and food environment surveys, along with attendance data). Trained research assistants (RAs) and study staff administer all instruments and assessments according to the written study protocol. At baseline, there were 174 participants enrolled from Wave 1 schools and 1008 from Wave 2 schools. Baseline measurements were conducted in the fall/early winter of Year 1 (Wave 1 – February-March, 2015; Wave 2 – September 2015-February 2016). Short-term measurements were conducted at the end of the first school year (Wave 1 – May-June 2015; Wave 2 – April-June 2016) and post-intervention measurements will be conducted approximately 18 months after baseline at the end of the second school year (Wave 1 – March-April 2016; Wave 2 – April-June 2017). At time of enrollment, participants are assigned a unique 5-digit code which is used in place of name or other identifiers to link participant to all their study data. The study project manager maintains an electronic, password-protected list linking participant with their unique ID.

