## Study design - overview

The FLEX Study is a cluster randomized controlled trial. Participating schools were clustered by location within the state and school district. Schools within each district were randomly assigned to receive a school-based PA intervention (*100 Mile Club* or *Just Move*) or assigned to be a control school. Third and fourth grade students were enrolled and are being followed for two school years (Fig. 1). Data are collected at three time points: baseline (fall, school year 1), short-term (spring, school year 1; 5–6 months post-baseline) and long-term post-intervention (spring, school year 2; ≈1.5 years post-baseline). The study occurred in two waves, the first beginning during the 2014–2015 school year (*n* = 6 schools) and the second wave during the 2015–2016 (*n* = 18 schools) school-year. Due to unforeseen weather circumstances and school cancellations in Winter 2015, additional student participant recruitment beyond the initial six schools was put on hold until the following school year. The investigative team determined that these schools would be designated as Wave 1. Approval for the study was obtained from the Tufts University IRB (Medford, MA) and additionally from individual school districts where required.

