## Primary outcomes

### Physical activity

Waist-worn tri-axial accelerometers are used to objectively measure participants’ physical activity (Actigraph accelerometers, models GT3X+ and wGT3X-BT, ActiGraph, LLC, Pensacola, FL) and have been validated and calibrated for use among children [26]. Study staff instruct each participant how to wear the accelerometer. Participants are asked to wear accelerometers during all waking hours, except when bathing or swimming, for 7 consecutive days. Accelerometers are initialized to store activity counts beginning at 00:00:01 on the first day the child will wear the device; data will be processed using a 15-s epoch. To support wear-time compliance, participants are also given a paper calendar-style tracking log on which they are instructed to write down the time they put the accelerometer on each morning and the time they remove it before bed each night. The log also asks participants to self-report any days they were ill during the wear week, as well as any sports or physical activities they played during the wear week and their favorite sports/physical activities. In addition, weather data are collected from the National Oceanic and Atmospheric Administration (NOAA) [27], and the high temperature (continuous) and precipitation (binary: yes/no) are recorded for each day accelerometers are worn. Data are collected from the weather station nearest to the participating school.

Accelerometer data will be categorized into minutes of sedentary, light, moderate and vigorous activity using thresholds developed specifically for children [28]. In-school and out-of-school time MVPA will be extracted. In-school hours will be calculated for each participant based on specific start and end times of the school day for each day the accelerometer was worn. Weekday out-of-school time will be calculated as the sum of before school time and after school time, accounting for school hours and average awake time.

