For statistical analyses, descriptive statistics for variables of interest will be compiled and tabulated. To test the effect of school-based PA programs on minutes spent in MVPA, we will compare *100 Mile Club* vs. control and *Just Move* vs. control as separate tests using mixed effects models. Outcomes of interest are changes in minutes of MVPA between midpoint vs. baseline and post-intervention vs. baseline. The key regression coefficient of interest is the intervention by time interaction term, which will indicate if the intervention is associated with a significant higher/lower change in MVPA across time compared to the control. The unique school identification number will be modeled as random intercepts to adjust for clustering. We will examine both unadjusted and adjusted (including covariates such as sex, race/ethnicity, weight status) regression coefficients of the respective program and conclude if the difference in MVPA minutes is statistically significant. A similar approach will be used to examine the impact of PA programming on academic/cognitive outcomes. All analyses will be performed using SAS 9.3 (Cary, NC, USA) and results with p-values less than 0.05 will be considered statistically significant.

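### Wave 2 baseline accelerometry runs from September to February, and the stated MVPA model names neither weather nor wear date and has no term for school-specific change over time, so its standard errors may be too small

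*Protocol article*

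**What the plan says.** **Measurement windows** (Data collection methods, Overview). Wave 1 baseline: "Baseline measurements were conducted in the fall/early winter of Year 1 (Wave 1 – February-March, 2015". Wave 2 baseline: "Wave 2 – September 2015-February 2016". Midpoint: "Short-term measurements were conducted at the end of the first school year (Wave 1 – May-June 2015; Wave 2 – April-June 2016". Post-intervention: "Wave 1 – March-April 2016; Wave 2 – April-June 2017". The Study design overview places the midpoint as "short-term (spring, school year 1; 5–6 months post-baseline".

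**Organisation of visits.** The Overview states that "child-level data collection takes place at each participating school during regular school hours at each of the three time points". It gives no order of schools and no matching of dates across arms.

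**Weather** (Primary outcomes, Physical activity). "the high temperature (continuous) and precipitation (binary: yes/no) are recorded for each day accelerometers are worn".

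**Model** (Sample size calculation and data analyses). The outcome is change in MVPA minutes from baseline to each follow-up. The coefficient of interest is the intervention-by-time interaction, each programme is tested against control, and school enters as a random intercept. On covariates: "We will examine both unadjusted and adjusted (including covariates such as sex, race/ethnicity, weight status) regression coefficients". Neither weather, wear date nor season is mentioned there.

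**Randomisation** (School recruitment & randomization). Schools are allocated in blocks of three, stratified by district.

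**The concern.** Season belongs to the week in which a school's children wear the device. If children's activity varies with season, a Wave 2 school with a winter baseline and a spring follow-up has a different seasonal part in its change from a school with a September baseline. The control arm removes the part that the arms share. It does not remove the part that arises because the schools of one arm happened, on average, to be measured earlier or later than those of another.

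That remainder varies by school and by time point. A random intercept for school absorbs a level that stays constant over time, not a shift between visits. Covariates such as sex, race/ethnicity and weight status describe children and cannot represent the date of a school's visit. At stake are the precision of the intervention-by-time estimate and whether its stated standard error is honest.

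**Working it through.** **1. The plan's own figures.** The documents attach no number to season. The nearest stated figure is the interval of 5-6 months from baseline to midpoint. Counting calendar months between the stated windows:

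| | Baseline to midpoint | Baseline to post-intervention |
|---|---|---|
| Wave 1 | about 2-4 months | about 12-14 months |
| Wave 2 | about 2-9 months | about 14-21 months |

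The stated midpoint interval cannot hold for every school, and in Wave 2 the spread comes mainly from the long baseline window. The planning figure for total daily MVPA (26 min per week, SD 40) does reproduce: 38 per arm at 80 % power and two-sided 5 %, against 39 stated.

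**2. Spread of baseline dates between arms.** Assumptions: dates uniform over 6 months and independent of arm; 24/3 = 8 schools per arm.
- SD of one school's date: 6/√12 = 1.73 months.
- SD of the difference between two arm means: 1.73 × √(2/8) = 0.87 month.

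**3. Error added to the contrast.** Let activity change by *s* min/day per month (assumed). The added standard error is 0.87 × *s*.

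| *s* | SD of school shift (1.73 × *s*) | Added SE of contrast |
|---|---|---|
| 0.5 | 0.87 | 0.4 min/day |
| 1 | 1.73 | 0.9 min/day |
| 2 | 3.46 | 1.7 min/day |

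If the Wave 1 schools, whose baseline window is narrow, contribute no spread and the waves are balanced across arms (6 Wave 2 schools of 8 per arm), the date SD becomes 1.73 × √(2/6) × 6/8 = 0.75 month. The added SE is then about 0.4, 0.75 and 1.5 min/day.

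**4. Scale.** The planning effect is 26/7 = 3.71 min/day. Detecting it with 80 % power needs a total SE of 3.71/2.80 = 1.33 min/day. At *s* = 1, season takes (0.87/1.33)² = 43 % of that variance; at *s* = 2 it exceeds the whole of it. No such comparison is possible for school-time MVPA, which was planned on a percentage of recess time.

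**5. Effect of leaving school-by-time variation out of the standard error.** Simulation with no programme effect, 8 schools per arm, 37 children per school and SD of a child's change 10 min/day (assumed). For comparison, (174 + 1008)/24 = 49 enrolled per school, and 49 × 0.75 = 37. The standard error used only child-level variation in change.

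| *s* | Mean bias | False-positive rate | Mean bias if one arm's baseline is 1 month later |
|---|---|---|---|
| 0 | 0 | 5 % | 0 |
| 0.5 | 0 | 9 % | 0.5 min/day |
| 1 | 0 | 18 % | 1.0 min/day |
| 2 | 0 | 39 % | 2.0 min/day |

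When dates are independent of arm, the mean bias is zero at every slope (at most 0.04 min/day in the simulation). What grows is the error rate.

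**The case against.** Four points can be made against this.

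*The covariate list is open.* It is introduced by way of example, and the article elsewhere gives diet quality and fitness a covariate role without repeating them in the analysis section. Recording weather for each wear day also suggests an intention to use it with MVPA. This stands: weather is unlisted, not excluded, and a fuller list may be in an analysis plan that was not at hand. It does not answer the point about random effects, because the article does state that part of the model.

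*The control arm handles season.* A reader might infer that the programme effect is confounded with season. The documents do not support that. Within-arm change mixes the two, but the tested quantity is a contrast with controls randomised within district. Systematic bias would need dates that differ by arm for a reason. Recruiting staff knew a school's arm once it joined, so this is possible, but nothing shows that it happened.

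*Silence on scheduling is not evidence of poor scheduling.* Visit order is operational detail, and recruitment went through districts, so schools of one block may well have been measured together. If so, the added error is smaller than computed above. The documents do not settle this.

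*The size is assumed.* This also stands. For example, a fall of 10 min/day from September to February, applied to 6 against 6 Wave 2 schools only, gives a 27 % chance of a shift of at least half the planning effect. Counting the Wave 1 schools lowers this to about 14-19 %. Neither figure should be quoted as a property of the trial.

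**Conclusion.** The point holds as one of precision and model specification, not of demonstrated bias. Wave 2 baselines span six calendar months, follow-ups fall in spring, and balance of wear dates across arms is not stated. Chance imbalance then adds school-level error to the intervention-by-time contrast, of about 0.4 to 1.7 min/day SE for slopes of 0.5 to 2 min/day per month. This assumes uniform dates independent of arm and about 8 schools per arm. The model as stated has no term that carries this error, so its standard errors may be too small. The seasonal slope and the SD of change in MVPA are not in the documents, so neither the added SE nor the false-positive rates can be narrowed further.

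**What to change.** In Sample size calculation and data analyses:
- Pre-specify wear-day (or wear-week mean) high temperature and precipitation, or wear date, as covariates in the MVPA model.
- Add a school-by-time random effect, so that school-specific change left after adjustment enters the standard error.
- Report baseline and follow-up wear dates by arm.

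Where feasible, measure the schools of one district block in the same or adjacent weeks at the remaining Wave 2 visit (April-June 2017). This limits further imbalance but cannot repair the completed baseline dates.

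The weather data are already being collected, so the analysis changes cost wording and a few degrees of freedom. Intervals will widen if schools do differ in their change, which is the correct result. The visit change costs slightly tighter scheduling.

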### Demographics

Demographic information was collected at baseline by paper-and-pencil questionnaire included with the recruitment packet and returned with informed consent documents. The 10-item questionnaire included questions on child’s date of birth, grade and age at time of enrollment, sex, race/ethnicity, maternal and paternal education levels, and free- or reduced-price lunch status. Parents/guardians were also asked to report whether or not their child has behavioral difficulties, such as learning, understanding or paying attention, or communicating [24] and whether their child was on an individualized education program (IEP). English language learner status will be obtained at the child-level from the Massachusetts DESE.

### Anthropometrics

Height and weight are measured in light clothing with shoes removed using a portable stadiometer (Model 213, Seca Weighing and Measuring Systems, Hanover, MD) and portable digital scale (Model 803, Seca Weighing and Measuring Systems, Hanover, MD). Height and weight are measured in triplicate to the nearest 1/8 in. and 0.1 kg, respectively. Body mass index (BMI) will be calculated (kg/m^2^) and converted into z-score using the Centers for Disease Control and Prevention (CDC) age- and sex-specific growth charts [25]. BMI percentiles are classified accordingly as: <5th percentile as underweight, 5th-85th percentile as normal weight, 85th-95th percentile as overweight, and ≥95th percentile as obese.

## Primary outcomes

### Physical activity

Waist-worn tri-axial accelerometers are used to objectively measure participants’ physical activity (Actigraph accelerometers, models GT3X+ and wGT3X-BT, ActiGraph, LLC, Pensacola, FL) and have been validated and calibrated for use among children [26]. Study staff instruct each participant how to wear the accelerometer. Participants are asked to wear accelerometers during all waking hours, except when bathing or swimming, for 7 consecutive days. Accelerometers are initialized to store activity counts beginning at 00:00:01 on the first day the child will wear the device; data will be processed using a 15-s epoch. To support wear-time compliance, participants are also given a paper calendar-style tracking log on which they are instructed to write down the time they put the accelerometer on each morning and the time they remove it before bed each night. The log also asks participants to self-report any days they were ill during the wear week, as well as any sports or physical activities they played during the wear week and their favorite sports/physical activities. In addition, weather data are collected from the National Oceanic and Atmospheric Administration (NOAA) [27], and the high temperature (continuous) and precipitation (binary: yes/no) are recorded for each day accelerometers are worn. Data are collected from the weather station nearest to the participating school.

Accelerometer data will be categorized into minutes of sedentary, light, moderate and vigorous activity using thresholds developed specifically for children [28]. In-school and out-of-school time MVPA will be extracted. In-school hours will be calculated for each participant based on specific start and end times of the school day for each day the accelerometer was worn. Weekday out-of-school time will be calculated as the sum of before school time and after school time, accounting for school hours and average awake time.

### Cognitive performance

Two cognitive assessments are administered one-on-one in a quiet area. A digit span test, with forward and backward subtests, is used to measure short-term memory, attention and concentration [29]. Digit span tests have been positively linked to PA [29, 30]. In the test, the administrator orally presents number lists of increasing length to the participant, and the participant is asked to repeat these digit spans back in the same order either forward or backward (for forward and backward subtests, respectively.)

A Stroop Color-Word test [31] is administered to assess inhibitory control and selective attention, aspects of cognitive function that have been positively linked with PA and fitness in previous studies [30, 32]. The test includes both a congruent task and an incongruent task, each lasting 45 s. Participants are first given the congruent task in which they are presented with a set of 100 color words printed in the *same* color ink as each word (ex. the word “*red*” is printed in red ink). They are asked to read these words aloud and complete as many as possible in 45 s. After completing this task, they are given the incongruent task, in which they are provided another set of 100 color-words printed in a *different* color ink (ex. the word “*red*” is printed in green ink). Participants are asked to identify and say aloud the color of the ink rather than the word, completing as many as possible in 45 s. The test is scored by calculating a ratio of items completed correctly to total number of items completed in 45 s.

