**Methods:**

Twenty-four public elementary schools from low-income, ethnically diverse communities around Massachusetts were recruited and randomized to receive either *100 Mile Club®* (walking/running program) or *Just Move™* (classroom-based PA program) intervention, or control. Schoolchildren (grades 3–4, approximately 50 per school) were recruited to participate in evaluation. Primary outcome measures include PA via 7-day accelerometry (Actigraph GT3X+ and wGT3X-BT), cognitive assessments, and academic achievement via state standardized test scores. Additional measures include height and weight, surveys assessing psycho-social factors related to PA, and dietary intake. School-level surveys assess PA infrastructure and resources and intervention implementation. Data are collected at baseline, mid-point (5–6 months post-baseline), and post-intervention (approximately 1.5 years post-baseline). Demographic data were collected by parents/caregivers at baseline. Mixed-effect models will test the short- and long-term effects of both programs on minutes spent in MVPA, as well as secondary outcomes including cognitive and academic outcomes.

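### The Stroop score is accuracy alone, so interference that shows as slowing on a speeded task cannot affect it

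*Protocol article*

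**What the plan says.** In the protocol article, the Cognitive performance section under Primary outcomes says the Stroop Color-Word test "is administered to assess inhibitory control and selective attention". On structure: "The test includes both a congruent task and an incongruent task, each lasting 45 s". Both tasks are speeded and each offers 100 items. For the congruent task, "They are asked to read these words aloud and complete as many as possible in 45 s". For the incongruent task, "Participants are asked to identify and say aloud the color of the ink rather than the word, completing as many as possible in 45 s".

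Scoring is given in one sentence: "The test is scored by calculating a ratio of items completed correctly to total number of items completed in 45 s". It does not say whether there is one ratio per task or one over both, and it names no comparison between the tasks.

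The analysis section adds nothing on the score: "A similar approach will be used to examine the impact of PA programming on academic/cognitive outcomes". Table 1 lists "Cognitive function (Digit Span and Stroop Color-Word tests" among the primary outcome measures, collected at all three time points. The abstract instead describes the models as testing MVPA "as well as secondary outcomes including cognitive and academic outcomes".

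**The concern.** When a child is told to get through as much as possible in a fixed time, difficulty can show in two ways: more errors, or fewer items reached. The stated ratio keeps the first and removes the second by dividing by the number attempted. On the incongruent task, a child who suppresses the printed word successfully but slowly shows interference as lost output, and the score cannot register it.

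The congruent task is the natural reference for separating interference from general speed, but the stated rule gives it no such role.

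At stake is the reading of a null result. If a programme changed how quickly children resolve the colour-word conflict without changing their error rate, this score would show nothing. The trial could then report no effect on inhibitory control partly because of how the test was scored.

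**Working it through.** The document gives no Stroop mean, SD, effect or sample size, so there is no figure to reproduce. The check applies the stated rule to assumed counts. All item counts below are illustrations; only the rule, the 45 s limit and the 100 items per task come from the document.

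**Rule.** Score = C / N, where C is the number correct and N the number attempted in 45 s. With accuracy p, C = pN, so the score is pN / N = p. N cancels, so the score does not depend on output.

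**Speed.** Incongruent task, output doubled at the same accuracy:

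| Accuracy p | Attempted N | Correct C = pN | Score |
|---|---|---|---|
| 1.00 | 20 → 40 | 20 → 40 | 1.00 → 1.00 |
| 0.98 | 20 → 40 | 19.6 → 39.2 | 0.98 → 0.98 |
| 0.95 | 20 → 40 | 19 → 38 | 0.95 → 0.95 |
| 0.90 | 20 → 40 | 18 → 36 | 0.90 → 0.90 |

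Correct output doubles in every row and the score does not move.

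**Reference task.** Two children with very different slowing between tasks:

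| | Congruent | Incongruent | Per-task scores | Congruent minus incongruent, correct items | Pooled score |
|---|---|---|---|---|---|
| Child 1 | 100/100 | 19/20 | 1.00 and 0.95 | 100 − 19 = 81 | 119/120 = 0.992 |
| Child 2 | 60/60 | 57/60 | 1.00 and 0.95 | 60 − 57 = 3 | 117/120 = 0.975 |

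Scored per task, the two children are identical, and so is the difference between their two accuracies (0.05 each). Scored over both tasks, the child who slows far more gets the higher score, because the many congruent items dominate the denominator. The unresolved choice between per-task and pooled scoring therefore changes the result, and neither choice recovers the slowing.

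**The case against.** A reader might infer that the score does not measure inhibitory control at all. The document does not support that. On the incongruent task, reading the word instead of naming the ink is itself a failure of inhibition and counts as an error, so accuracy there carries part of the intended signal.

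A reader might also infer that the trial never contrasts the tasks. The text states no contrast, but it is one sentence in a condensed article. Two per-task ratios could be compared without contradicting it, and a fuller document not shown may define such a comparison. This objection stands in part: the silence about the contrast is not the defect. It does not rescue the stated ratio, because a contrast of two accuracies still ignores speed.

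A third tempting inference is that the rule ranks children wrongly on inhibition, for example by placing 20 of 20 (1.00) above 57 of 60 (0.95). Without congruent counts that does not follow. If the congruent counts were 22 and 100, incongruent minus congruent would be 20 − 22 = −2 and 57 − 100 = −43, and the first child would still rank better. The example shows greater output, not better inhibition.

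A ceiling near 1 is plausible for an accuracy score, but no score distribution is given and its presence cannot be shown.

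Reach is also limited. The Aims put MVPA first, the sample size rests on MVPA alone, and the Stroop is one of two cognitive tests. The MVPA conclusions are untouched.

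**Conclusion.** The concern holds as a poorly fixed scoring rule. The article commits to a score that is accuracy alone, for a test whose instructions in both tasks reward output. That the score is unaffected by the number attempted follows from the rule itself and needs no assumption about the data. The protocol also needs to settle per-task or pooled scoring and give the congruent task a stated role.

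The supportable description is an incomplete and possibly insensitive measure of inhibitory control, not an invalid one. How much sensitivity is lost depends on how far interference in these children shows as slowing rather than errors, and on how close accuracy sits to 1. The document gives neither, so no size can be put on the loss. The point deserves correction because Table 1 lists the test as a primary outcome measure, although the abstract calls cognitive outcomes secondary.

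**What to change.** State that each task is scored as the number of correct items in 45 s. Make the Stroop outcome the incongruent correct count, adjusted for the congruent correct count from the same visit. Keep the accuracy ratio, formed separately for each task, as a supportive measure. Because the congruent count at follow-up is itself measured after the programmes have started, report the programme effect on each task's count alongside the adjusted result.

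The cost is small but not zero:

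- No new testing is needed, since the ratio already requires correct and attempted counts. Rescoring does depend on those counts having been kept by task.
- This is a change of outcome definition during the trial. By the article's schedule, Wave 1 post-intervention measurement (March-April 2016) and Wave 2 midpoint measurement (April-June 2016) came before publication in October 2016. Wave 2 post-intervention measurement (April-June 2017) was still ahead. The change must be dated and justified, preferably without sight of results by arm.
- The new score is not pure either. The congruent task is word reading and the incongruent task is ink naming, so the adjusted count still mixes interference with the difference in speed between reading and naming. The report should say so.
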